**Methods/Design:**

We will assign patients with moderately severe to severe COPD to either continuous exercise or interval exercise using a stratified randomisation. Patients will follow 12–15 exercise sessions during a comprehensive inpatient respiratory rehabilitation. Primary end point for effectiveness is HRQL as measured by the Chronic Respiratory Questionnaire (CRQ) two weeks after the end of rehabilitation and secondary endpoints include additional clinical outcomes such as functional exercise capacity, other HRQL measures, patients' experience of physical exercise as well as physiological measures of the effects of physical exercise such as cardiopulmonary exercise testing. Including expected drop-outs, we will need 52 patients per group to show differences corresponding to the minimal clinically important difference of the CRQ. Outcome assessors and investigators involved in data analysis will be blinded to group assignment until analyses have been carried out.

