### Clinical outcome measures

#### Chronic Respiratory Questionnaire (CRQ)

We will use the CRQ[23] to measure HRQL changes during rehabilitation. The CRQ is a widely used disease-specific instrument to assess symptoms of COPD patients [24-26] We will use the self-administered German CRQ.[27,28] with standardised dyspnoea questions.[29] that we have developed and validated in earlier studies. Patients will complete the CRQ in the Klinik Barmelweid at baseline, at the end of the rehabilitation, two and 12 weeks thereafter when they have returned to their home environment.

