### Effectiveness

Our null hypothesis is that high intensity continuous exercise is of clinically superior effectiveness compared with interval exercise to improve HRQL (δ ≥ 0.5 in CRQ domains scores). The alternative hypothesis is that interval exercise is not of clinically inferior effectiveness compared with high intensity continuous exercise.

In the primary analysis, we will calculate the raw difference and 95% confidence intervals between groups in the mean follow-up score for the CRQ domains 2 weeks after completion of the respiratory rehabilitation programme. In an additional analysis, we will adjust for the base-line score and the four stratification variables using an analysis of covariance. We will use independent t-test to compare the change scores between groups.

We will also use the confidence interval approach as recommended for equivalence and non-inferiority trials[13] We will establish non-inferiority of interval exercise if the point estimate and its 95% confidence interval for difference between the change scores of the continuous and interval exercise group is smaller than the a priori determined boundary of clinical equivalence (see figure 3). If the 95% confidence intervals lie outside the boundaries of clinical equivalence we will establish clinical superiority of one exercise protocol.

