**Figure 3 F3:**
[figure not shown]
Illustration of the confidence interval approach to interpret results from randomised trials. The horizontal line indicates the difference between CRQ change scores between study groups. ± 0.5 points represent the predefined boundaries of equivalence. If the whole confidence interval is on the right of 0.5 points, interval exercise is not inferior to continuous exercise. If the whole confidence interval is within boundaries the two exercise protocols are of clinically equivalent effectiveness (upper three confidence intervals). Note that there can be a statistically significant difference between study groups but without any clinical relevance.

Most methodologists and statisticians agree that the boundaries of equivalence should be defined as the minimal important difference and below the differences observed in previous trials comparing active to control treatments.[13,39] The minimal important difference is "the smallest difference in score in the outcome of interest that informed patients perceive as important, either beneficial or harmful, and which would lead the clinician to consider a change in the management"[40]. Therefore, the minimal important difference of our two main outcome measures for effectiveness have been established empirically and are around 0.5 for the CRQ domains scores [41-44] and 53 meters for the six-minute walk test[45]. A recent meta-analysis showed that respiratory rehabilitation with physical exercise leads to improvements of 50 meters in the six-minute walk test. Therefore we lower the boundaries for equivalence to ± 45 meters in order to have boundaries that are below the differences observed in previous trials comparing active to control treatments.[13,39]

We will repeat the analysis with calculations of raw and adjusted differences for all other clinical and physiologic outcome measures and test for significant differences between groups using independent t-test if data are distributed normally.

We will use both intention to treat and per protocol analysis to show equivalence in either case as recommended by others[13,39,46,47]

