#### Sample size

For calculating the required sample size, we use the formula for comparison of 2 means: n = [A + B]^2 ^* 2 * SD^2^/DIFF^2^, where n = the sample size required in each group (double for total sample), SD = standard deviation of the outcome variable, DIFF = size of desired difference between groups. A and B depend on the desired significance level and desired power, respectively.

We base our sample size calculations on the CRQ. We used empirical data from our previous trial.[27], where we applied similar inclusion criteria for patients with COPD undergoing respiratory rehabilitation, to estimate variability of the CRQ (standard deviation of the CRQ domain scores between 0.8 and 1.2). A clinically sensible way to determine the size of desired difference between groups (DIFF in formula above) is based on the minimal important difference (0.5 on the scale from 1 to 7 for the CRQ)[41-43,48] A sample size of 44 patients in each group will allow showing a difference of 0.5 in CRQ scores between the groups, assuming a standard deviation of 0.8, with a power of 90% at a significance level of 5% (one-sided). Assuming a drop out rate of 15%.[27], the total minimal sample size increases to 104. This sample size will also allow detecting a difference of 45 meters in the six-minute walking test scores between the two treatment groups with a power of 95% at a significance level of 5% (one-sided) assuming a drop out rate of 15%.

A priori sample size calculations usually provide only rough estimates. Therefore, we will recalculate sample size during the study when we have the data for 30 patients in each group. To this end, we will re-assess the standard deviation of the outcome variables and, if necessary, adjust the sample size accordingly (without breaking the randomisation code).

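### The effectiveness analyses as worded make no use of the end-of-rehabilitation CRQ for patients lost by two weeks, which costs precision and leaves a possible bias of unknown direction

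*Protocol article*

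**What the plan says.** The abstract (Methods/Design) sets the endpoint: "Primary end point for effectiveness is HRQL as measured by the Chronic Respiratory Questionnaire (CRQ) two weeks after the end of rehabilitation". Under Effectiveness, the primary analysis is the "raw difference and 95% confidence intervals between groups in the mean follow-up score for the CRQ domains 2 weeks after completion" of the programme. A second analysis follows: "In an additional analysis, we will adjust for the base-line score and the four stratification variables using an analysis of covariance". Change scores are to be compared by t-test, and the non-inferiority rule in the same section is applied to the difference in change scores against a boundary of 0.5. The section ends by promising both analysis sets: "We will use both intention to treat and per protocol analysis".

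The section on the CRQ says that patients complete it "at baseline, at the end of the rehabilitation, two and 12 weeks thereafter when they have returned to their home environment".

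Under Sample size: "A sample size of 44 patients in each group will allow showing a difference of 0.5 in CRQ scores between the groups", with an SD of 0.8. Then: "Assuming a drop out rate of 15%.[27], the total minimal sample size increases to 104". The article does not say when the 15% are lost or from which group.

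**The concern.** Each named effectiveness analysis needs a two-week score. A patient who finishes the inpatient stay and is then lost should already have a baseline CRQ and an end-of-rehabilitation CRQ, the latter taken about two weeks before the primary value. As worded, neither contributes for that patient.

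Two things are at stake. First, precision is given up even if losses are random. Second, in a population with severe disease, patients who are not seen after discharge may well differ from those who are. If the pattern differs between groups, a comparison of observed cases is biased, and the promised intention-to-treat analysis rests on about 44 of 52 patients per group. In a non-inferiority trial, such a bias can produce a false claim or hide a true one.

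**Working it through.** **1. The plan's own figure.** From Sample size: difference 0.5, SD 0.8, one-sided 5%, power 90%.

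n = (1.645 + 1.282)² × 2 × 0.8² / 0.5² = 43.85, so 44 per group. 44 / 0.85 = 51.8, so 52 per group and 104 in total. Both figures reproduce. Conversely 52 × 0.85 = 44.2, so the calculation counts about 8 patients per group as lost to the analysis.

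**2. Bias of an observed-case comparison.** Let D = continuous minus interval. Non-inferiority is claimed if the upper 95% limit of D is below 0.5, so a negative bias favours the claim. Let d be the share missing in a group and G the mean of observed minus the mean of missing patients.

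Bias in D = d_C × G_C − d_I × G_I

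| Loss C / I | G_C / G_I | Bias in D |
|---|---|---|
| 15% / 15% | equal | 0 |
| 20% / 10% | 0.5 / 0.5 | +0.05 |
| 10% / 20% | 0.5 / 0.5 | −0.05 |
| 15% / 15% | 0.8 / 0.3 | +0.075 |
| 15% / 15% | 0.3 / 0.8 | −0.075 |

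The sign depends on quantities that the article does not give.

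**3. Simulated size.** From the protocol: 52 per group, SD 0.8, 15% lost in each group. Assumed: correlation 0.5 between baseline and later visits, 0.7 to 0.8 between end of rehabilitation and two weeks, and all losses after discharge. There were 6,000 trials per setting. Loss depends on a low end-of-rehabilitation score in one group and is random in the other.

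| Estimator | Size of bias, correlation 0.7 | Size of bias, correlation 0.8 |
|---|---|---|
| Raw two-week score | 0.099 | 0.110 |
| Change score | 0.029 | 0.042 |
| Analysis of covariance, completers | 0.065 | 0.077 |
| Repeated measures, likelihood | 0.001 | 0.002 |

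The bias favours interval exercise if the score-dependent loss is in the interval group, and continuous exercise if it is in the continuous group. It is zero if the dependence is the same in both. By step 2, a raw bias of 0.099 to 0.110 at 15% loss means that lost patients score 0.66 to 0.73 below retained ones (0.099 / 0.15 and 0.110 / 0.15).

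**4. Error rate on the change-score rule.** The change-score estimate has SD 0.170. At a true D of 0.5, false non-inferiority = Φ(bias towards interval / 0.17 − 1.96).

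- No bias: 2.5%.
- Score-dependent loss in the interval group: Φ(0.029/0.17 − 1.96) = 3.7%; Φ(0.042/0.17 − 1.96) = 4.3%.
- Score-dependent loss in the continuous group: Φ(−0.029/0.17 − 1.96) = 1.7%; Φ(−0.042/0.17 − 1.96) = 1.4%.

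**5. Unequal loss rates, raw two-week score.** A separate simulation (correlation 0.8, poorer patients more likely to be lost in both groups) compared observed cases with a regression estimator using the end-of-rehabilitation CRQ.

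| Loss C / I | False non-inferiority, observed cases | With the end-of-rehabilitation CRQ |
|---|---|---|
| 15% / 15% | 2.5% | 2.3% |
| 20% / 10% | 0.8% | 2.1% |
| 10% / 20% | 5.9% | 2.7% |

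At 20% / 10% and no true difference, power was 75% with observed cases and 86% with the extra score. Bias against the claim also has a price.

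**6. Precision under random loss.** SD of the estimate: raw 0.171, completer analysis of covariance 0.148 to 0.149, repeated measures 0.142 to 0.145.

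- Repeated measures against analysis of covariance: 1 − (0.145/0.149)² = 5%; 1 − (0.142/0.148)² = 8%.
- Repeated measures against raw: 1 − (0.145/0.171)² = 28%; 1 − (0.142/0.171)² = 31%.
- Analysis of covariance against raw: 1 − (0.149/0.171)² = 24%; 1 − (0.148/0.171)² = 25%. Most of the gain over the raw comparison is therefore baseline adjustment.

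**The case against.** The strongest reply is that the article nowhere excludes patients without a two-week score. It names the contrasts and promises intention to treat. Rules for missing values are commonly left to a full protocol or analysis plan, which is not shown, and inflating 44 to 52 is routine. This stands in part: observed cases is an inference, and silence on imputation is no fault. But the article does choose its estimators, and as named they leave out a scheduled measurement.

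A reader might infer that the bias runs towards non-inferiority. The documents do not support that. It needs score-dependent loss that is heavier or more selective in the interval group. The Background expects interval exercise to be better tolerated, which, if anything, points to more loss from the continuous group and a bias against the claim.

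A reader might also take the raw-score bias of 0.10 and compute Φ(0.10/0.17 − 1.96) = 8.5% false non-inferiority. That figure belongs to the raw follow-up contrast. The stated non-inferiority rule uses change scores, where the same adverse scenario gives 3.7 to 4.3%.

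Finally, a single-time-point comparison is a legitimate choice, and the extra score cannot rescue everyone. Patients who leave during the stay may have no end-of-rehabilitation CRQ, and relapse after discharge need not be predicted by it. Both points stand and limit the gain.

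**Conclusion.** The point holds as a cheap improvement, not as a demonstrated error. The named analyses make no use of the end-of-rehabilitation CRQ for patients who complete the stay and are then lost. Read as observed cases, they lose some precision and leave a possible bias of unknown sign in the intention-to-treat result.

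Its size is modest. The bias is zero when score-dependent loss is alike in both groups. When it occurs in one group only, it is about ±0.10 (raw score) or ±0.03 to 0.04 (change score), against a margin of 0.5. In the adverse direction the change-score rule goes from 2.5% to about 4% false claims. Under random loss, the variance gain over completer analysis of covariance is 5 to 8%.

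These figures rest on SD 0.8 and 15% loss, both from the protocol. They also rest on correlations that it does not give, on loss explained by observed scores, and on all loss falling after discharge. If part of the 15% leave earlier, the gains are smaller.

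**What to change.** State that the two-week difference that decides non-inferiority comes from a likelihood-based repeated-measures model:

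- outcomes: CRQ at end of rehabilitation, two weeks and 12 weeks;
- covariates: baseline CRQ by visit and the four minimisation factors;
- unstructured covariance between visits;
- patients: all randomised with any post-baseline CRQ.

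Add one sensitivity analysis that lowers missing interval-group values by up to 0.5, the margin. The raw difference can stay as a supporting result.

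The cost is analysis wording only, since every score is already scheduled. There is a small downside. The model assumes that losses are explained by observed scores. The sensitivity analysis tests departures unfavourable to interval exercise. The model helps little for patients who leave before the end-of-rehabilitation CRQ.

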Exercise tests to establish training intensity should consider the exercise mode. Meyer et al. studied interval exercise in several studies [14-16] in patients with chronic heart failure who show similar patterns of physical deconditioning in terms of clinical manifestation as well as morphological and metabolic abnormalities [17-19] Meyer et al. used a steep ramp test to determine short time muscular maximum exercise capacity[14], which reflects muscle strength and anaerobic capacity, both relevant for interval exercise.

Meyer et al. also assessed different ratios of work/recovery phases (1:2; 1:4 and 1:6) and found that with these ratios and relatively short phases of high intensity exercise (10–30 seconds), lactate did not accumulate presumably because of lactate elimination during the recovery phases.[14] Interval exercise with these ratios was therefore recommended as high intensity aerobic exercise modes for patients who do not sustain continuous exercise.

Because of the scarcity of evidence on the comparative effectiveness of interval exercise for COPD patients, additional trials are needed.[1,6] Our primary objective is to assess if interval exercise is not of inferior effectiveness compared to continuous exercise of high intensity to improve HRQL and exercise capacity in patients with moderately severe to severe COPD and the secondary objective is to evaluate if interval exercise is better tolerated by COPD patients.

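### Non-inferiority is stated over several CRQ domains, but the decision rule and the 90% power fit a single score, and the six-minute walk has conflicting status

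*Protocol article*

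**What the plan says.** **CRQ.** The abstract states: "Primary end point for effectiveness is HRQL as measured by the Chronic Respiratory Questionnaire (CRQ) two weeks after the end of rehabilitation". It names no domain or total score. In the Effectiveness section the null hypothesis is that continuous exercise is clinically superior "to improve HRQL (δ ≥ 0.5 in CRQ domains scores", and the primary analysis takes the group difference "in the mean follow-up score for the CRQ domains 2 weeks after completion of the respiratory rehabilitation programme". Both are plural. The decision rule is singular: "We will establish non-inferiority of interval exercise if the point estimate and its 95% confidence interval for difference between the change scores" falls within the boundary. The Figure 3 legend likewise describes one CRQ difference against ±0.5.

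**Sample size.** The calculation is based on the CRQ, with a difference of 0.5, SD 0.8, 90% power and one-sided 5%. This gives 44 per group, raised to 104 in total for 15% drop-out. The same section reports domain SDs between 0.8 and 1.2 and plans to re-assess the SD once 30 patients per group have data.

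**Six-minute walk.** The abstract says that "secondary endpoints include additional clinical outcomes such as functional exercise capacity". The primary objective at the end of the Background is non-inferiority "to improve HRQL and exercise capacity in patients with moderately severe to severe COPD". The text after Figure 3 refers to "our two main outcome measures for effectiveness have been established empirically", meaning the CRQ and the walk test, and gives the walk its own boundary of ±45 m. The Sample size section gives it its own power statement.

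**The concern.** Followed as written, the plan gives several CRQ verdicts but one overall claim, and nothing links them. If some domains clear the margin and others do not, the document does not say whether interval exercise has been shown to be non-inferior on HRQL. The natural reading of a null stated over the domain scores is that all of them must clear the margin, but the stated power was not computed for that rule. The walk test adds to the uncertainty, because a reader cannot tell whether it is part of the main claim.

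This is more than detail left to an analysis plan. The article itself fixes a primary analysis, a decision rule and a sample size that do not fit together, and it ranks the walk test in different ways.

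**Working it through.** **Inputs from the protocol article.** Margin 0.5 (Effectiveness, Figure 3 legend). SD 0.8, with a domain range of 0.8 to 1.2; 90% power; one-sided 5%; 44 per group; 15% drop-out (Sample size). The decision is by 95% confidence interval, which is one-sided 2.5% against the margin (Effectiveness).

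**Assumptions, because the article does not give them.** Number of domains k = 2 to 4, common correlation ρ = 0.5 to 0.9, equal SD 0.8, true difference 0.

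**Step 1: reproduce the plan's figure.** n = (1.645 + 1.282)² × 2 × 0.8² / 0.5² = 43.85, rounded up to 44 per group. With drop-out, 44 / 0.85 = 51.8, so 52 per group and 104 in total. The plan's numbers are correct for one score.

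**Step 2: power for one domain with 44 per group.** SE = 0.8 × √(2/44) = 0.1706, and 0.5 / 0.1706 = 2.931.
- One-sided 5%: Φ(2.931 − 1.645) = 90%.
- 95% interval: Φ(2.931 − 1.960) = 83%.

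The step from 90% to 83% has nothing to do with the number of domains. It comes from sizing at one-sided 5% and deciding at one-sided 2.5%.

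**Step 3: power if every domain must clear the margin.** Simulation of correlated normal estimates, 400,000 draws per setting, 44 per group, SD 0.8:

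| k | ρ | One-sided 5% | 95% interval |
|---|---|---|---|
| 2 | 0.5 | 83% | 74% |
| 2 | 0.9 | 87% | 79% |
| 4 | 0.5 | 74% | 61% |
| 4 | 0.9 | 84% | 75% |

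As a check on the method, independence should give powers of the single-domain figure. For one-sided 5%, 0.901² = 81% and 0.901⁴ = 66%, and the simulation agrees.

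**Step 4: risk if any one domain sufficed.** True difference at the margin in every domain:

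| k | ρ | Nominal 5% | Nominal 2.5% |
|---|---|---|---|
| 2 | 0.5 | 9% | 4.5% |
| 2 | 0.9 | 7% | 3.5% |
| 4 | 0.5 | 14% | 8% |
| 4 | 0.9 | 9% | 4.6% |

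**Step 5: larger SDs.** With k = 4 and SDs spread over 0.8, 0.93, 1.07 and 1.2, all-domain power is 46% to 59% at one-sided 5% and 33% to 46% under the 95% interval (ρ = 0.5 to 0.9). Most of this is the SD. At SD 1.2 one domain alone has 62% at one-sided 5% and 50% under the 95% interval.

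**The case against.** **A condensed article may leave combination rules to the full protocol or analysis plan.** This is fair for silence alone. It does not cover an analysis over several domains beside a one-difference rule and a one-score sample size, all stated in the same article.

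**A reader might infer an inflated false-positive rate.** The document does not support that as a fact. No passage says one favourable domain is enough, and an all-domain rule needs no alpha adjustment. The figures in Step 4 are conditional on a rule the plan never adopts.

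**A reader might also infer that power is far below 90% because of the several domains.** This is only partly supported. The domain count and correlation are assumed. At one-sided 5% and high correlation the loss is moderate (84% for four domains at ρ = 0.9). The lowest figures also contain the alpha mismatch and larger SDs, and the planned SD re-estimation may offset the latter.

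**The plan has safeguards.** Data analysis provides for coded groups and two manuscript versions agreed before unmasking, so it would be too strong to say the authors would choose the favourable result. But coding hides which group is which, not which domains met the margin, and re-estimating the SD changes the sample size without defining success.

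**The walk-test conflict is partly wording.** The effectiveness null and primary analysis concern only HRQL, the sample size is based on the CRQ, and the term main outcome appears where margins are justified. The documents do not make the walk a co-primary endpoint. Still, the primary objective includes exercise capacity and the abstract makes it secondary, so the tension is real.

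**Conclusion.** The point holds as an internal mismatch. The null and primary analysis cover several CRQ domains, the decision rule covers one difference, and 44 per group gives 90% power for one score. For a claim needing every domain, power is about 74% to 87% at one-sided 5%, or about 61% to 79% under the planned 95% interval. Both ranges assume 2 to 4 domains, correlation 0.5 to 0.9 and SD 0.8. In the second range, the part from 90% down to 83% belongs to the separate alpha mismatch. Larger SDs would lower power further unless the re-estimation raises the sample size.

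Error inflation (about 7% to 14% at nominal 5%, or 3.5% to 8% at nominal 2.5%) would arise only under an any-domain rule, which is not in the text. The six-minute walk has conflicting status across the abstract, the Background objective and the Effectiveness section.

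**What to change.** In the Effectiveness section, choose one of two rules before any outcome data are compared by group:

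1. State that non-inferiority on HRQL is claimed only if the confidence limit clears 0.5 in every CRQ domain. No alpha adjustment is needed. State the number of domains and restate the power for this rule in the Sample size section, at the level used for the decision.
2. Name one primary CRQ score and make the other domains supportive.

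In either case, align the Background objective and the text after Figure 3 with the abstract, so that the six-minute walk is secondary throughout. Testing the walk only after the CRQ claim succeeds is one possible arrangement, but this point does not require it.

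**Cost.** The change is wording, plus a lower stated power under the first rule. Restating it needs no extra enrolment. Restoring 90% would: with four domains, SD 0.8 and independence as the worst case, about 66 per group at one-sided 5% or 79 at one-sided 2.5%, before drop-out. The second rule keeps the present single-score calculation, subject to the chosen score's SD and the alpha mismatch.
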